
### Supplement design

2.20

Patients will be clustered into distinct groups based on the similarity of their baseline gut microbiota composition, clinical markers, and dietary patterns. Dimensionality reduction techniques, e.g., principal component analysis (PCA) or uniform manifold approximation and projection (UMAP) will be applied to reduce noise and identify key features driving interindividual variability. Subsequently, unsupervised clustering algorithms (e.g., k-means, hierarchical clustering, or model-based clustering) will be employed to classify patients into homogeneous subgroups. These patient clusters will serve as the basis for subsequent supplement design, analyses of intervention response and biomarker discovery. The dietary supplement will be formulated by selecting two or three food groups or food components that meet the highest number of predefined criteria. The selection criteria will be: (1) components positively associated with, or predictive of, a greater number of protective variables or markers of healthier status in Alzheimer’s patients; (2) components negatively associated with, or predictive of, a greater number of disease-related markers.

The rationale for designing a supplement rather than recommending dietary modifications is to minimize disruption of habitual dietary patterns, thereby maximizing adherence to the intervention and reducing caregiver burden. In addition to supplement formulation, dietary recommendations may be provided to reduce or eliminate food components associated with unfavorable biomarkers (e.g., predictors of elevated LPS levels or other parameters of disease progression). If lack of physical activity is identified as a relevant factor, tailored recommendations will also be considered according to the patients’ physical condition.

The selection of supplement ingredients will be based on analysis of patients’ dietary intake to ensure that nutrient levels do not exceed recommended intakes for the study population and that established diet quality indices are maintained. Individual dietary preferences and restrictions will also be taken into account. Food components will preferentially be included in powdered form to facilitate integration into common foods (e.g., soups, yoghurts, purees), while vitamins and minerals, if selected, will be administered as liquid or pill formulations. Dosage will be determined according to dietary reference values and available scientific literature supporting the beneficial health effects of the selected components.

### Statistical analysis

2.21

The analysis of the obtained data will be carried out using the statistical software SPSS version 29.0. The mean and standard deviation, or the median and interquartile range, will be used to describe each parameter, depending on the data distribution. The assumption of normality will be assessed using the Shapiro–Wilk test. All continuous outcomes will be analyzed using linear models adjusting for the baseline value of the outcome and a set of covariates: age, sex, education level, comorbidity burden, concomitant medication, physical activity level, nutritional status, and perceived stress. Study site will be included as a fixed effect. For outcomes with repeated measures (e.g., pre/post within participants), we will use linear mixed-effects models with a random intercept for participant and treatment group (personalized supplement vs. control) as the main fixed effect. Where a single post-intervention endpoint is analyzed, an ANCOVA (post value as dependent variable; treatment as factor; baseline outcome and covariates as regressors) will be used. An intention-to-treat (ITT) approach will be employed to evaluate the effectiveness of the intervention. The ITT analysis will include all participants initially randomized, regardless of whether they completed the intervention as planned, withdrew, or deviated from the protocol. For gut microbiota analysis, RStudio (v. 1.4.1106, RStudio, 2022) will be used. The phyloseq R package (51) will be employed to compare different estimates of alpha diversity and to plot the relative abundance of microbial groups. The vegan R package (52) ^1^will be used to compute beta diversity, i.e., inter-sample diversity, visualized through Principal Coordinates Analysis (PCoA) based on the Bray–Curtis dissimilarity index. The significance and effect of treatments on the bacterial community (beta diversity) will be evaluated using PERMANOVA implemented in the vegan package. Differences will be considered statistically significant when the *p*-value is less than the alpha level (0.05). For microbiome, functional profiles and untargeted metabolomics, we will use MaAsLin2, a multivariable linear modeling framework designed for meta-omics data analysis (53) with appropriate normalization/transformations, adjusting for the same covariates listed above. Participant ID will be specified as a random effect for longitudinal analyses. For multiple comparisons, the Benjamini–Hochberg correction will be applied to control the false discovery rate. To address multiplicity, two complementary approaches will be applied depending on the type of outcomes. For a small number of primary or key secondary outcomes (e.g., plasma LPS, total SCFAs), we will apply the Bonferroni correction. For high-dimensional exploratory domains (microbiota taxonomic and functional profiles, untargeted metabolomics, and dietary intake variables), *p*-values will be adjusted using the Benjamini–Hochberg procedure to control the false discovery rate (FDR).

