### Sample size calculation

2.4

To calculate the sample size, the method used to test the association between the abundance of a microbiota taxon and exposure to a variable or group of variables was applied (23). The bacterial genus *Odoribacter* was selected for this purpose, as its abundance has shown a significant role in predicting AD (24). The mean and standard deviation of the relative abundance of this genus were 0.26 ± 0.42 in healthy individuals and 0.77 ± 0.77 in patients with AD, according to data obtained directly from the authors of Liang et al. (25). The pooled standard deviation was 0.6533, and the calculated effect size was: (0.77–0.26)/0.6533 = 0.7806. Considering this effect size, and assuming a significance level (*α*) of 0.05 and statistical power (1 − *β*) of 0.80, the formula used for calculating the sample size was: 
n=[2×(z₁⋅α/2+z₁⋅β)2]/(effect size)2
. Substituting the values yields a required sample size of 25 individuals per group. To account for an estimated 20% dropout rate, the final sample size was adjusted to 30 participants per intervention group. Accordingly, the cross-sectional stage (stage 1) will be conducted with *n* = 60 participants per group, which will provide robustness to detect differences between healthy individuals and patients with AD. In the subsequent intervention phase, which will be carried out exclusively in patients with AD, these 60 individuals will be randomized into two arms: one receiving the designed supplement and the other a standard supplement. The aims of this pilot intervention are to: (i) estimate trends and effect sizes of the intervention on the microbiota and clinical parameters, (ii) evaluate the feasibility and acceptability of the intervention protocol in this vulnerable population, and (iii) collect preliminary data to power a future definitive randomized controlled trial. The intervention will last 3 months, as the aim is to obtain preliminary results in a pilot context.

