### Sociodemographic and lifestyle data

2.7

Participants’ demographic information, including age, sex, and ethnicity, as well as socioeconomic factors such as household income, number of household members, and education level will be collected. Lifestyle habits, including alcohol consumption, smoking, and contact with animals, will also be recorded. Clinical variables such as time since disease onset, age at diagnosis, and the affected brain regions will be documented, along with cerebrospinal fluid (CSF) biomarkers such as Abeta42 and phosphorylated Tau levels. Behavioral symptoms and pharmacological treatments (e.g., cholinesterase inhibitors, memantine, neuroleptics, and trazodone) will also be assessed. To evaluate dietary habits in both patients and healthy controls, a comprehensive dietary assessment will be conducted. The following validated tools will be used: a food frequency questionnaire (FFQ) (29) assessing habitual intake over the past year, a 3-day food record collected during the same week as microbiota sampling, and the 14-item Mediterranean Diet Adherence Screener (MEDAS) (30). Food intake data will be analyzed using DIAL software (version 3.15.0.0) (31) to determine intake of macronutrients, micronutrients, fiber, and other bioactive compounds, including: complex carbohydrates and simple sugars, animal and plant-based proteins, saturated, monounsaturated, and polyunsaturated fats, soluble and insoluble fiber, ethanol, and water- and fat-soluble vitamins. Physical activity will be assessed using the International Physical Activity Questionnaire for the Elderly (IPAQ-E) (32) and the Clinical Frailty Scale (CFS) (33).

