The knowledge generated by this project could also serve as the basis for the development of new products in the food and pharmaceutical industries, where the analysis methodology could be applied to customize products based on specific consumer or patient characteristics. However, several limitations of the present study should be acknowledged. First, the reliance on self-reported dietary and lifestyle data introduces potential biases, including recall and social desirability bias. Second, adherence to the personalized supplement may be challenging, especially among individuals with AD, who may resist changes to their routine. Third, the use of caregivers as the healthy control group instead of community-based controls. Although this choice increases feasibility and facilitates adherence to study procedures, it may introduce potential biases related to caregiver stress, shared environment, and lifestyle similarities with patients. Fourth, potential issues may arise related to supplement formulation, its stability, or potential interactions with medications, all of which will need to be addressed during study implementation. Fifth, although the study aims to consider multiple factors (e.g., individual characteristics, microbiota, and diet), the influence of unaccounted confounding variables may affect the study outcomes. Sixth, the relatively short intervention period of 3 months limits the ability to evaluate long-term outcomes, including prevention or disease modification. Finally, despite biomarker confirmation, the AD population remains heterogeneous, which may influence microbiota profiles and intervention responses.

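### The single covariate list does not fit the cross-sectional AD–healthy comparison: it has no patient–caregiver pair term and leaves the medication covariate open to AD-specific drugs

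*Protocol article*

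**What the plan says.** Section 2.21 states one model for every continuous outcome. It adjusts for the outcome's own baseline value, for "age, sex, education level, comorbidity burden, concomitant medication, physical activity level, nutritional status, and perceived stress", and for site as a fixed effect. For microbiome, functional and metabolomic data, MaAsLin2 is run "adjusting for the same covariates listed above". The only contrast written out is personalized supplement against control. The random effects are at participant level only: an intercept for repeated measures and, for MaAsLin2, "Participant ID will be specified as a random effect for longitudinal analyses".

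Section 2.3 makes the microbiota difference between healthy controls and AD participants part of the primary outcome. Section 2.4 gives that cross-sectional stage 60 participants per group.

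On medication, section 2.7 records "pharmacological treatments (e.g., cholinesterase inhibitors, memantine, neuroleptics, and trazodone" among the clinical variables. Section 2.21 does not say which drugs its medication covariate covers.

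On controls, section 2.1 allows healthy caregivers to serve as control subjects. The limitations in section 3 describe caregivers as the healthy control group and name possible bias from "caregiver stress, shared environment, and lifestyle similarities with patients". The mitigation paragraph that follows promises that these factors will be documented and handled in the analysis, without saying how.

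**The concern.** The list reads as if written for the randomised comparison and then extended to everything. In stage 1 it meets three difficulties.

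- **Pairing.** A patient and the caregiver who lives with or looks after that patient are not independent observations for diet or gut microbiota. A model that treats them so computes the wrong variance for the AD–healthy contrast.
- **Medication.** A covariate that includes cholinesterase inhibitors or memantine is close to a marker of AD status. With such a term, only patients who do not take the drugs inform the AD coefficient.
- **Baseline value.** In a cross-sectional comparison there is no earlier value of the outcome to adjust for.

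At stake is the precision, and with the medication term also the meaning, of a contrast that belongs to the primary outcome and feeds the supplement design.

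**Working it through.** **Inputs from section 2.4.** Two-sided alpha 0.05 and power 0.80 ("assuming a significance level (*α*) of 0.05 and statistical power (1 − *β*) of 0.80"); means 0.77 and 0.26; pooled SD 0.6533; 60 per group in stage 1.

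**The plan's own figure.** d = (0.77 − 0.26)/0.6533 = 0.78. n = 2 × (1.960 + 0.842)² / 0.7806² = 25.8, so 26 per group; the plan states 25. Then 25 × 1.2 = 30 per arm, as stated. This calculation assumes two independent groups and no covariates. On the same basis, 60 per group gives 98.9% power at d = 0.78 (noncentral t, 118 df).

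**Pairing.** The within-pair correlation ρ and the share of controls paired with an enrolled patient, f, are not in the document; both are assumed. With n per group:

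- variance if independent: 2σ²/n
- true variance: (2σ²/n)(1 − fρ)
- overstatement: 1/(1 − fρ)

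| f | ρ | Overstatement | Actual size of a nominal 0.05 test |
|---|---|---|---|
| 1 | 0.2 | 1.25 | 0.028 |
| 1 | 0.3 | 1.43 | 0.019 |
| 0.5 | 0.2 | 1.11 | 0.039 |
| 0.5 | 0.3 | 1.18 | 0.034 |

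The standard error is too wide, so the test rejects less often than its nominal level.

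**Medication.** Let p be the share of patients on an AD-specific drug (assumed), with none among controls. The squared correlation between AD status and drug use is p/(2 − p), so the variance inflation is 1/(1 − p/(2 − p)) = (2 − p)/(2 − 2p).

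A direct check gives the same answer. At p = 0.8, 12 patients are untreated. The AD coefficient then has variance σ²(1/12 + 1/60) = 0.100σ², against σ²(2/60) = 0.033σ² without the drug term, a factor of 3.0.

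Power is at d = 0.78 with 120 − 11 = 109 df (intercept, AD status, eight covariates, site).

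| p | Variance factor | Equivalent n per group | Power |
|---|---|---|---|
| no drug term, no covariates | 1.0 | 60 | 99% |
| 0.5 | 1.5 | 40 | 93% |
| 0.7 | 2.2 | 28 | 82% |
| 0.8 | 3.0 | 20 | 69% |
| 0.9 | 5.5 | 11 | 44% |

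These figures isolate the drug term: they give no credit for variance explained by the other covariates. They also use alpha 0.05 per test. The false-discovery correction planned for taxa would generally make the threshold stricter and the powers lower.

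**The case against.** **The stage-1 model may be in an unseen analysis plan.** The sentences around the list concern pre/post measures and treatment, so the baseline term can be read as meant for the trial alone. MaAsLin2 reuses the covariates, which the sentence lists apart from the baseline value. That makes the baseline point minor. It does not remove the rest: section 2.21 states its rule for all continuous outcomes, and a rule already fixed is not a detail left for later.

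**Pairing is not established.** Caregivers only may be controls, nothing requires a control's own patient to be enrolled, and no pairing rate is given. Perceived stress is already a covariate and deals with one of the biases section 3 names. This stands as a limit on size. Stress does not stand in for a shared environment, though, and the promise in section 3 has no matching term in section 2.21. A reader might infer that unmodelled pairing produces false positives. The formula shows the reverse for positive correlation.

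**AD drugs are an inference.** The covariate could be a drug count or non-AD classes. Neuroleptics and trazodone are not AD-specific, and nothing says controls do not take them. This stands, so the medication limb is conditional. A reader might infer that stage 1 loses most of its power. At 50% use it keeps 93%, and at 70% it is still above 80%.

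**The same list in the randomised comparison.** A reader might infer that it is too long there as well: ten terms besides treatment, with about 60 × 0.8 = 48 completers. The figures do not settle that. At d = 0.78, power is 75% with no covariates. With the ten terms it is 64% if they explain nothing, 74% if they explain 20% of the variance and 85% if they explain 40%. The plan also specifies intention-to-treat on all 60 and calls the trial a pilot. No change to the stage-3 list follows.

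**Conclusion.** The point holds for stage 1 only. Section 2.21 applies one list to all continuous outcomes without a model suited to the AD–healthy contrast.

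- **Pairing:** where patient and caregiver are both enrolled, the analysis as written overstates the variance, by 25–43% at an assumed correlation of 0.2–0.3 with full pairing, and less with partial pairing. The cost is precision, not type I error.
- **Medication:** if the covariate includes AD-specific drugs, the variance rises 1.5 to 5.5 times over an assumed 50–90% use in patients and none in controls, and power falls from 99% to between 93% and 44%. The document gives neither the coding nor the rate of use, so the loss may be small or large.
- **Baseline value:** it has no meaning in stage 1; this is a matter of wording.

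The remaining covariates are not at fault. In a non-randomised contrast, education, comorbidity, physical activity, nutritional status and stress are plausible confounders, and nothing here justifies removing them.

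**What to change.** State a separate stage-1 model in section 2.21:

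- Leave out the baseline value of the outcome. Keep the listed confounders and site.
- Limit the medication covariate to drugs that are not AD-specific, and say how it is coded. Examine AD-specific drugs in a sensitivity analysis within the AD group.
- Record a patient–caregiver pair ID at enrolment and use it as a random effect in the linear and MaAsLin2 models. A participant without an enrolled partner takes an ID of their own.
- Where PERMANOVA is used for the AD–healthy contrast, use the pair as a permutation block for paired participants. Unpaired participants cannot be permuted within a block, so say how they are handled.

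Leave the stage-3 list as it is.

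The cost is a few sentences and one extra data field. The downside is interpretive: the stage-1 contrast becomes AD including its usual drugs, and reports must describe it so.

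### Holm's step-down procedure would give the key outcomes the same 5% family-wise error control as the planned single-step Bonferroni correction, with never less and sometimes more power

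*Protocol article*

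**What the plan says.** Section 2.21 (Statistical analysis) sets two multiplicity rules. For the key outcomes: "For a small number of primary or key secondary outcomes (e.g., plasma LPS, total SCFAs), we will apply the Bonferroni correction". No step-down version is mentioned, so single-step Bonferroni is the plain reading: with m outcomes, each is tested at 0.05/m. The two named outcomes are examples, and m is not stated. For the high-dimensional domains, p-values are to be "adjusted using the Benjamini–Hochberg procedure to control the false discovery rate (FDR"); this point does not touch that rule.

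Section 2.4 (Sample size calculation) sizes the groups on the relative abundance of one bacterial genus in AD patients against healthy people, at a two-sided 0.05 with no multiplicity adjustment and 80% power. It reports that "The pooled standard deviation was 0.6533" and that the effect size is 0.7806, giving 25 per group. After an allowance for 20% dropout, "the final sample size was adjusted to 30 participants per intervention group". The same section calls the intervention phase a pilot whose first aim is to estimate trends and effect sizes.

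**The concern.** Single-step Bonferroni holds every outcome to 0.05/m, even after another outcome in the family has been rejected. Holm tests the smallest p-value at 0.05/m, the next at 0.05/(m−1), and so on, stopping at the first failure. Both keep the family-wise error at or below 5% whatever the correlation between outcomes.

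The two differ most when several outcomes move together. Section 1 (Introduction) describes success in those terms: a healthier microbiota, fewer AD-related taxa and changed AD-related biomarkers. The sample size makes no allowance for a multiplicity correction, so the choice of correction bears directly on the power left for these outcomes.

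**Working it through.** **Inputs.** From section 2.4: d = 0.7806, two-sided alpha 0.05, power 0.80, 30 per arm, 20% dropout. From section 2.21: Bonferroni, alpha 0.05. Assumed, because the article does not give them: family size m = 2 (also m = 4); treatment effects of 0.78, 0.5 and 0.3 SD; correlation between outcomes 0 to 0.3; 30 × 0.8 = 24 per arm with data; unadjusted two-sample t-tests.

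**The plan's own figure.** n = 2 × (1.960 + 0.842)² / 0.7806² = 25.76 per group. The article states 25; rounding up would give 26. Then 25 × 1.2 = 30, as stated. The figure reproduces closely enough to use d = 0.7806 as a benchmark.

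**Power of one t-test, 24 per arm** (noncentral t, 46 degrees of freedom, noncentrality d × √(24/2)):

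| Shift | at 0.05 (A) | at 0.025 (B) |
|---|---|---|
| 0.78 SD | 0.754 | 0.651 |
| 0.5 SD | 0.396 | 0.289 |
| 0.3 SD | 0.175 | 0.110 |

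**Where the procedures differ when m = 2.** Only when the smaller p is at most 0.025 and the larger lies between 0.025 and 0.05. For p = 0.010 and 0.040, Bonferroni compares both with 0.025 and rejects one. Holm compares 0.010 with 0.025, then 0.040 with 0.05, and rejects both.

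**Two independent outcomes, both shifted.** Power per outcome is B under Bonferroni and B + (A − B) × B under Holm.
- 0.78 SD: 0.651 becomes 0.651 + 0.103 × 0.651 = 0.718, a gain of about 7 points.
- 0.5 SD: 0.289 becomes 0.289 + 0.107 × 0.289 = 0.320, about 3 points.
- 0.3 SD: 0.110 becomes 0.110 + 0.065 × 0.110 = 0.117, under 1 point.

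Both detected at 0.78 SD: B² = 0.651² = 0.424 under Bonferroni; A² − (A − B)² = 0.754² − 0.103² = 0.558 under Holm. With correlation 0 to 0.3, simulation gives 42–47% and 55–59%.

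At least one detected at 0.78 SD: 1 − (1 − 0.651)² = 0.878 under both. The first step is the same test, so this never differs when all outcomes are affected.

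**Only one of two outcomes affected (0.78 SD).** Its power goes from 0.651 to 0.651 + 0.103 × 0.025 = 0.654. The chance of a false rejection on the unaffected outcome goes from 0.025 to 0.025 + 0.025 × 0.651 = 0.041, still below 0.05.

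**Four outcomes, all shifted by 0.78 SD (simulation, correlation 0 to 0.3).** Per outcome, about 55% becomes about 65%. All four detected: 9–17% becomes 28–39%.

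**Sensitivity.** A separate simulation used normal test statistics and correlations up to 0.5. With m = 2 and 30 per arm at 0.78 SD, power per outcome goes from 78.3% to 83.0–84.1%. With 25 per arm at 0.3 SD it goes from 12.0% to 12.7–13.5%, so the gain there reaches 1.5 points at correlation 0.5. In no simulated data set did Holm fail to reject something that Bonferroni rejected.

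**The case against.** The strongest reply is that nothing here is wrong. Bonferroni is a valid and conservative correction, the article does not contradict it, and preferring another valid method is a matter of taste. The first two parts stand: a reader might infer that the planned analysis is faulty, and it is not. The last part stands only in part. As a test, single-step Bonferroni is dominated by Holm, and the article does fix the method instead of leaving it open.

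A reader might also infer that effects on second and later outcomes are simply lost, and for no return. The documents do not support that. Bonferroni tests every outcome, and the two procedures part only in the narrow region shown above. With two independent outcomes that region covers 2 × 0.103 × 0.651 = 13% of trials at 0.78 SD and 2 × 0.065 × 0.110 = 1.4% at 0.3 SD. Bonferroni also has simple matching simultaneous intervals, which have value in a pilot meant to estimate effect sizes, and a lower actual error when some effects are real.

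The third objection concerns size, and it stands. The 0.78 SD is a difference between patients and healthy people on one genus, not an effect of one supplement against another on LPS or SCFAs. Section 2.21 plans ANCOVA or mixed models with covariates, so the absolute powers above do not describe the planned analysis. Section 3 (Discussion) says that the study is not meant to be definitive, so it would be too strong to say that the trial depends on this power. None of this reverses the direction: under no assumption does Holm reject less or exceed 5%.

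**Conclusion.** The point holds as a cheap, optional improvement and not as an error. For the family in section 2.21, Holm gives the same 5% family-wise guarantee and can declare a further effect once one has been declared. The per-outcome gain ranges from under 1 point to about 10 points. It is largest if all outcomes move by about 0.78 SD and the family is larger, and negligible if effects are small or only one outcome responds. These figures rest on an assumed family size, assumed effects and 24 per arm. That Holm never has less power needs none of these assumptions.

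**What to change.** In section 2.21, for the same key outcomes, name *the Holm step-down procedure (family-wise alpha 0.05, two-sided)* in place of Bonferroni. Report Holm-adjusted p-values, and show 95% confidence intervals labelled as unadjusted for multiplicity.

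The cost is a few words in the plan, with no extra data or participants. There are two drawbacks to accept. Simultaneous intervals that match Holm are less simple than Bonferroni's, so an unadjusted interval may exclude zero beside a non-significant adjusted p-value; the label is there for that reason. And with one of two outcomes truly unaffected, the actual false-rejection rate rises from about 2.5% to about 4%, within the 5% limit.
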